#### Data collection

2.2.3

Data collection of Study Part 2 will start in February 2023 and measurements will be completed approximately in July 2025. Study part 2 begins as soon as the participant takes up the aftercare health behavior after rehabilitation. For each week we will assess the engagement in the aftercare health behavior. The measurement occasions of the psychological variables will depend on the days and time of the participant's aftercare health behavior. While intention and anticipated affect will be assessed before the aftercare health behavior, remembered affect and habit will be measured after the aftercare health behavior. Motivation will be assessed at the beginning of the assessment period of Study Part 2 and at the end. Questionnaires will be sent via the application MovisensXS to participants' smartphones. The duration of Study Part 2 depends on the chosen aftercare health behavior and on the participants' willingness to maintain it. A duration of 12 weeks is currently scheduled with the option to extend the duration up to 24 weeks (e.g., IRENA lasts 24 weeks). Figure 2 shows the measurement occasions dependent on the aftercare health behavior.

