#### Study Part 2: study of psychological determinants of aftercare health behaviors

1.1.2

Study Part 2 adopts a mixed-methods design consisting of quantitative and qualitative methods. The objective of the quantitative component is to analyze the influence of specific psychological determinants on aftercare health behaviors. This includes examining how intention, anticipated affect, experienced affect, habit, and motivation influence the adoption and maintenance of aftercare health behaviors. The qualitative study aims to analyze the conditions that affect success or failure in completing an aftercare health behavior. By exploring patients' experiences and challenges, this part of the study seeks to gain knowledge about why patients either follow through with their aftercare health behavior or drop out.

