#### Sampling and participants

2.2.1

Participants of Study Part 1 are eligible for Study Part 2, if they plan to implement an aftercare health behavior on a regular basis after their rehabilitation program ends (e.g., participation in an after-care program). The data collection for this study part has not started yet. Researchers will contact participants that gave their written consent to participate in Study Part 2 at t_0_ or t_1_. Participants will inform the researchers about their planned aftercare health behavior (i.e., the specific days during the week and the time planned to execute the behavior). In the quantitative part of Study Part 2, psychological determinants of the aftercare health behavior will be assessed using Ambulatory Assessment. Researchers will send short questionnaires via the application movisensXS to the participants on different measurement occasions during the week dependent on the selected days and times of the aftercare health behavior. Participants will also be asked whether they performed the planned behavior and to state the reasons if not. Missing planned physical activity sessions are not a reason for dropout, as long as the participant will plan to continue with the health behavior. In the qualitative part of Study Part 2, participants of the quantitative part will be interviewed, which either successfully implemented the aftercare health behavior or failed to implement it on a regular basis. Both groups will be interviewed to gather more information about the reasons that contributed to their success or failure.

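### Study Part 2 observation is conditional on uptake and continued willingness, so planners who never start and weeks after giving up have no stated quantitative follow-up

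*Protocol article*

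**What the plan says.** The objective (section 1.1.2) is to examine how the determinants "influence the adoption and maintenance of aftercare health behaviors". Participants of Study Part 1 are eligible (Sampling and participants, 2.2.1) "if they plan to implement an aftercare health behavior on a regular basis after their rehabilitation program ends", so entry depends on a plan and not on a first session.

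Data collection (2.2.3) sets the start: "Study part 2 begins as soon as the participant takes up the aftercare health behavior after rehabilitation". On the end it says: "The duration of Study Part 2 depends on the chosen aftercare health behavior and on the participants' willingness to maintain it". The next sentence adds: "A duration of 12 weeks is currently scheduled with the option to extend the duration up to 24 weeks".

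On missed sessions, section 2.2.1 says: "Participants will also be asked whether they performed the planned behavior and to state the reasons if not". It continues: "Missing planned physical activity sessions are not a reason for dropout, as long as the participant will plan to continue with the health behavior". Section 2.2.3 also has engagement assessed for each week.

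Data analysis (2.2.4) uses multilevel models, citing their flexibility with unbalanced data and missing values, and latent growth curve models. It does not say how weeks after a discontinuation are treated.

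**The concern.** Adoption and maintenance are the outcomes, yet both ends of the observation window appear to be set by those same outcomes. If the window opens at uptake, everyone observed has taken the behaviour up, and the contrast between planners who start and planners who do not is absent from the quantitative data. If it closes when willingness ends, the failure event also ends data collection.

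The second point bears on how missing values may be handled. Weeks that are absent because the person gave up are not ordinary gaps, since their outcome value is in effect known to be not performed. A model that treats them as ignorable would draw its later weeks mainly from people who kept going. This is decided at data collection: an analysis plan can choose how to code recorded weeks, but it cannot recover weeks that nobody asked about.

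**Working it through.** **Inputs.** From section 2.2.1: f = 0.10, alpha = 0.05, power 0.80, r = 0.50, 12 repeated measures, 72 participants, 10% dropout per week over 12 weeks, 226 recruited. From section 2.2.3: 12 weeks scheduled.

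**The plan's own figures.** For the within-between interaction, lambda = f²·N·m/(1 − r) = 0.01 × 72 × 12 / 0.5 = 17.28. With two groups (assumed, as the number is not stated) the power at N = 72 is 0.808, so 72 reproduces. The 226 is matched by 72 × 1.1^12 = 225.97. Dividing by retention gives 72 / 0.9^11 = 229.4 or 72 / 0.9^12 = 254.9. The route to 226 is a separate matter, and the present point does not depend on it.

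**How much follow-up the plan expects to lose.**
- Remaining after 11 weekly losses: 226 × 0.9^11 = 70.9, about 71, so 155 are gone (69%).
- Remaining after 12 weekly losses: 226 × 0.9^12 = 63.8, about 64, so 162 are gone (72%).
- Person-weeks observed, with everyone present in week 1 and 11 losses after it: 226 × (1 − 0.9^12)/0.1 = 226 × 7.176 = 1,622.
- Person-weeks scheduled: 226 × 12 = 2,712. Observed share: 1,622 / 2,712 = 60%. Unobserved: 2,712 − 1,622 = 1,090.

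Let s be the share of unobserved person-weeks that follow a discontinuation of the behaviour. The number that are really not performed is then s × 1,090. The protocol gives no value for s, so the range is 0 to 1,090.

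**What the passages provide for each kind of participant.**
- *Takes up the behaviour, misses sessions, still plans to continue.* Stays in the study. Non-performance and its reason are recorded (2.2.1), and engagement is assessed weekly (2.2.3). This case is covered.
- *Plans the behaviour, never starts.* Eligible under 2.2.1, but the start condition in 2.2.3 is never met, so no observation period is stated. Section 2.2.1 ties prompts to planned days and times, which could imply an earlier start. The two sections then need to be reconciled.
- *Starts, then gives up.* The exemption from dropout in 2.2.1 lasts only while the person plans to continue, and 2.2.3 lets duration depend on willingness. Read together, giving up appears to end participation. No later quantitative assessment is described.
- *Withdraws or loses contact while still performing.* Dropout in the usual sense. Nothing described separates this from the previous case in the 10% weekly figure.

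The interviews do not fill the gap. Interviewees come from the quantitative part, and those who stopped form a purposive group of at least eight.

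**The case against.** A reader might infer that Part 2 sees people only while they perform the behaviour. The text contradicts this: prompts follow planned times, missed sessions are logged with reasons, a yes/no intention item is asked beforehand, and engagement is assessed weekly. Lapses are visible, and data from the weeks before someone stops are used.

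A reader might also conclude that adoption cannot be studied at all. The protocol does not define adoption as a first session. The abstract contrasts people who adopt with people who discontinue, and interview group A is people who have integrated the behaviour into everyday life. In that sense adoption can be studied after a start. Figure 2, which shows the measurement occasions, is not available here and may clarify the start rule.

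The willingness clause can also be read as governing only the extension from 12 towards 24 weeks. That reading is fair and would remove part of the problem, but the text does not say so, and the dropout sentence in 2.2.1 points the other way. Nor does any passage state that weeks after stopping are treated as missing at random; that is an inference, and outcome coding is commonly left to an analysis plan. Whether those weeks are collected at all is a design matter and remains open.

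It is tempting to put a size on the distortion. If people still in the behaviour performed in 85% of weeks, and a share of leavers had stopped, true week-12 engagement would be 0.85 × (1 − (1 − 0.282) × share): 85%, 55% or 24% for shares of 0, one half and 1. The 85% appears nowhere in the protocol and the share is unknown, so the range restates its assumptions. It also concerns prevalence of engagement, whereas the aim is the effect of determinants, for which no bias has been calculated.

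Finally, it is planned that "remembered affect and habit will be measured after the aftercare health behavior". Missed sessions therefore have no such value, but that is inherent in the constructs, and nothing in 2.2.4 rules out using the previous session's value. It is not an error.

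**Conclusion.** The concern holds in a limited form. The start rule in 2.2.3 does not fit the planning-based eligibility in 2.2.1 or an objective that includes adoption, and people who plan but never start have no stated observation period. After someone gives up, no quantitative follow-up is described, so later missingness is plausibly informative. This second part rests on reading the dropout sentence and the willingness clause together, since neither states outright that stopping ends participation.

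The amount of follow-up at stake is large on the plan's own dropout assumption: about 40% of scheduled person-weeks. How much of that is discontinuation cannot be derived, so no bias in any determinant effect is claimed. This is an inexpensive design improvement worth making before collection begins, because the missing information could not be obtained afterwards.

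**What to change.** Reconcile 2.2.1 and 2.2.3 as follows.

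1. Start each person's window at the first session date they report as planned, whether or not that session takes place.
2. Keep the scheduled 12 weeks for everyone. Treat any extension towards 24 weeks as additional.
3. After a stated discontinuation, continue a single weekly performed yes/no item to the end of the 12 weeks, and count those weeks as not performed.
4. Count only withdrawal from the study or loss of contact as dropout, and record it separately from giving up the behaviour.

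Using habit and remembered affect from the last performed session as lagged predictors is optional and not part of the correction.

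The cost is a change to the app trigger and a small weekly burden for people who have stopped, some of whom may not answer. That it is cheap assumes, as 2.2.1 states, that Part 2 collection had not begun. Section 2.2.3 gives a start in February 2023, before the September 2023 start of Part 1, and that date should be checked at the same time.

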**Figure 2 F2:**
[figure not shown]
Study design of Study Part 2.

##### Intention

2.2.3.1

Intention is a complex construct with two components: decisional intention reflects the direction of the intention (toward aftercare health behavior or toward an alternative behavior), while intention strength represents the commitment to enact behavior in that direction [intensity of intention, (38)]. Decisional intention to perform the aftercare health behavior will be assessed with the item “Do you intend to do … (specific behavior)” and can be answered with “yes” or “no”. If “yes”, intention strength will be measured with the item “To what extent do you intend to do … (specific behavior)”, and can be answered on a seven-point response scale ranging from 1 (very low) to 7 [very high, (38)].

##### Perceived behavioral control

2.2.3.2

Perceived behavioral control will be assessed with one item measuring the level of ones perceived control related to showing the aftercare behavior: “It is within my control to participate in … (e.g., the IRENA session).” Participants will respond to a Likert scale ranging from 1 (strongly disagree) to 7 (strongly agree). Similar items have been part of previous studies measuring perceived behavioral control to predict health behavior showing good reliability (39, 40).

##### Anticipated affect

2.2.3.3

An adapted version of the Feeling Scale is used to measure anticipated affect. The Feeling Scale is a well-established single-item measure of affective valence (41). The adapted version of the Feeling Scale asks participants about their expectations of how they will feel during the aftercare health behavior. The response scale ranges from −5 (very bad) to +5 (very good). Similar versions of the Feeling Scale have already been used in previous studies (42, 43).

##### Remembered affect

2.2.3.4

Remembered affect will be measured shortly after the aftercare health behavior with the Empirical Valence Scale (EVS). The EVS consists of a single item to measure how well participants felt while performing a health behavior (44). The visual analogue scale ranges from −100 (most unpleasant imaginable) to +100 (most pleasant imaginable) and thirteen verbal anchors (e.g., strongly, barely, slightly) are placed throughout the scale. The EVS has been used in previous studies to measure remembered affect (45).

##### Habit

2.2.3.5

Habit will be assessed after the aftercare health behavior was shown with one item:

“Attending the … (e.g., today's IRENA session) was something I did automatically.” The response scale consists of four items on a five-point Likert scale ranging from 1 (strongly disagree) to 5 (strongly agree). The item is based on the Self-Report Behavioral Automaticity Index (SRBAI) and measures the automaticity of the behavior as a central feature of habit (46) and has been used in a previous study (47).

##### Motivation

2.2.3.6

Motivation is assessed using the German version of the Behavioral Regulation Exercise Questionnaire-2 (BREQ-2), which consists of 19 items with a 5-point response format (48). It covers five different types of motivation: (1) amotivation, (2) external regulation, (3) introjected regulation, (4) identified regulation, and (5) intrinsic motivation. In addition to the individual manifestations of motivation, the Relative Autonomy Index (RAI) can also be calculated, which represents a person's degree of self-determination in relation to a behavior (48). Cronbach's alpha is 0.60 for amotivation, 0.77 for external regulation, 0.77 for introjected regulation, 0.83 for identified regulation, and 0.88 for intrinsic regulation (49). In terms of validity, the subscales were found to correlate with each other consistent with the theory, and higher self-determined motivation was associated with an increased likelihood of engaging in health behavior (49).

#### Data analysis

2.2.4

In order to quantify the effects of psychological determinants on aftercare health behaviors, multilevel models will be calculated. The advantage of multilevel models in the analysis of repeated measures data is their flexibility in dealing with unbalanced data structures, nested samples (e.g., clustering in rehabilitation centers), and missing values (50). This modeling technique is particularly suited for analyzing data that is hierarchically structured, nested in treatment centers or involves repeated measures, thus allowing for the assessment of both individual and group-level variations (e.g., analysis of the influence of programs in different rehabilitation centers). In addition, latent growth curve models will be used to examine the relationships between the growth parameters of intentions, anticipated affect, experienced affect, habit, and aftercare health behaviors. This modeling approach facilitates an in-depth exploration of individual growth trajectories and their interrelations over time, offering valuable insights into the developmental aspects of health behaviors post-rehabilitation.

The interviews will be analyzed using reflexive thematic analysis. Specifically, the six-phase model (51) will be applied. In order to increase the trustworthiness of the analysis, the interviews will be analyzed independently by two persons. In addition, other researchers will serve as critical friends to contemplate alternative interpretations of the interviews (52). These researchers will provide independent perspectives and assist in exploring alternative interpretations, thereby enhancing the depth and credibility of our qualitative findings.

## Discussion

3

The aims of this study are (1) to evaluate the effectiveness and the durability of effects of orthopedic rehabilitation programs and (2) to gather a deeper understanding of how psychological determinants influence aftercare health behaviors.

Study Part 1 includes a three-year follow-up period after rehabilitation, which is much longer than most previous studies (9) and enables the evaluation of long-term effects. Additionally, a control period without treatment (i.e., before the rehabilitation program starts) is planned. In Study Part 2, the use of Ambulatory Assessment allows for data collection in daily life that is aligned with the time the participants execute their individual aftercare health behavior. In addition, an advantage of mixed methods designs is that qualitative data help explain results of quantitative data. Therefore, interviews with participants may provide additional information about how psychological determinants interact with the individual aftercare health behavior.

Possible challenges include the recruitment of patients prior to the start of the rehabilitation programs to build an adequate control group. Patients will receive the study material via post and a promotion letter of the rehabilitation center is supposed to increase the recruitment rate prior to rehabilitation. Furthermore, long follow-up periods with many measurement occasions often result in high drop-out rates and sample attrition (53). For that reason, researchers will send out reminders to fill out all questionnaires. Regarding Study Part 2, participants may change the aftercare health behavior they chose and switch time and dates when they plan to execute their behavior.

The importance of this research project lies in its comprehensive examination of two interrelated aspects vital to the field of rehabilitation: the effectiveness and durability of effects of rehabilitation programs (Study Part 1) and the psychological determinants of aftercare health behaviors that contribute to long-term health (Study Part 2). Although orthopedic rehabilitation programs in Germany seem to have positive effects on quality of life and work ability (9), the long-term impact of these treatments have not been evaluated yet. In addition, gaining knowledge about how health behaviors can be transferred into everyday life is of great importance to ensure the success of the rehabilitation. These insights hold significant potential for the optimization of rehabilitation programs, fostering lasting health behaviors after rehabilitation, and enhancing overall patient outcomes. Furthermore, the evidence-based refinements of rehabilitation programs suggested by this research could lead to more efficient resource allocation and reduced costs for the healthcare system. By linking clinical practice to patients' psychological determinants and personal experiences, the study contributes to a more patient-centered and economically sustainable approach for orthopedic rehabilitation.

## Trial status

The data collection of Study Part 1 started in September 2023.

## Ethics statement

The studies involving humans were approved by Karlsruhe Institute of Technology. The studies were conducted in accordance with the local legislation and institutional requirements. The participants provided their written informed consent to participate in this study.
